#### Secondary outcomes

Compare the ratio of progression into the clinical proteinuria period after intervention between the two groupsUrine microalbumin-negative conversion rate: the ratio of normal urinary microalbumin (< 20 μg/min) compared between the two groupsChange in GFR: change in the D-value and ratio of glomerular filtration rate (GFR) before and after treatment compared between the two groups. GFR calculated using the simplified MDRD formula: GFR (ml/min·1.73 m^2^) =186 × serum creatinine – 1.154 × age – 1.154 × [female × 0.742] × [Chinese × 1.233]Doubling rate of baseline creatinine value compared between the two groups after intervention

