**Methods/design:**

This trial is a 13-center, randomized, double-blind, placebo-controlled study. A total of 632 participants will be randomized in a 1:1 ratio to an experiment group (TSF plus losartan) and a control group (placebo plus losartan). The trial cycle will last 24 weeks. The primary outcome will be the change in the urine microalbumin–creatinine ratio from baseline to week 24. The secondary outcome will be the change in the rate of progression to the clinical proteinuria period after intervention, the rate of urine microalbumin negative conversion, the rate of normal urinary microalbumin, the doubling rate of the baseline creatinine value and the glomerular filtration rate between the two groups. Safety in medication will also be evaluated.

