### Participants

#### Diagnostic criteria

The diagnostic criteria for this trial will be set based on the American Diabetes Association guidelines [7], Chinese Diabetes Society guidelines [8], National Kidney Foundation Kidney Disease Outcomes Quality Initiative (NKF-KDOQI) guidelines [30] and Kidney Disease Improving Global Outcomes (KDIGO) 2012 Clinical Practice Guideline [31]. For a diagnosis of early-stage DKD, patients with DM will have to present the following conditions:
Diagnosed with type 2 diabetesPatients with type 2 diabetes with microalbuminuria and urinary microalbumin excretion rate (UAER)
For microalbuminuria, two repeated tests performed within 6 months will need to produce abnormal resultsUAER of 30–300 mg/24 h or urinary albumin-to-creatinine ratio (ACR) of 30–300 mg/g (mg/mmol)Have clinical manifestations of kidney diseases, such as edema, anemia, renal dysfunction, etc.

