### Outcomes

#### Primary outcomes

Urinary microalbumin (MAlb) is a critical indicator for the diagnosis of early renal impairment in diabetes mellitus. For early-stage DKD, the urinary microalbumin–creatinine ratio (ACR) will be a primary evaluation index. The change in ACR from baseline will be evaluated between the two groups, and the ACR will be compared at baseline and treatment endpoint (24 weeks) in each group.

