### Study visits and assessment

The intervention cycle will be 24 weeks, including a run-in period. After the research commences, visits will occur every 4 weeks during the study period. An overview of specific measurements and time points for data collection is presented in Table 1.

**Table 1 Tab1:** Measurement items and point of data capture

Visit project	Screening period/baseline	Visits 1–2, 4–5	Visit 3	Visit 6
Visiting time	–7 to 0 days	Medication 4, 8, 16, 20 weeks ±7 days	Medication 12 weeks ±7 days	Medication 24 weeks ±7 days
Collect basic medical history				
Sign informed consent	×			
Fill in general information	×			
Medical history and treatment history	×			
Determine inclusion and exclusion criteria	×			
Vital signs	×	×	×	×
Physical examination	×	×	×	×
Comorbidity and medication records	×	×	×	×
Monitoring and inspection				
Urine pregnancy test	×			
Glycosylated hemoglobin, blood lipids	×		×	×
Fasting blood sugar and blood pressure	×	×	×	×
Effectiveness observation				
Urinary microalbumin–creatinine ratio	×	×	×	×
Urinary microalbumin excretion rate	×	×	×	×
Serum creatinine	×	×	×	×
Glomerular rate filtration	×	×	×	×
24-h urinary microalbumin and 24-h urinary microalbumin quantification	×		×	×
Physico-chemical examination				
Routine blood test and routine urine test	×		×	×
Stool routine examination	×		×	×
Vital signs	×	×	×	×
ECG, liver and kidney function	×		×	×
Adverse event		×	×	×
Other work				
Random grouping	×			
Distribute drug and patient journal cards	×	×	×	
Recovery drugs, quantity statistics		×	×	×
Recycle patient’s diary card		×	×	×
End of study summary				×

*ECG* electrocardiogram

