### Statistical analysis

The statistical analysis of this study was completed by an independent statistician, and the detailed statistical analysis plan was formulated separately by a statistician before the inception of this trial and determined with the Principal Investigator. Three analysis sets will be used for assessment of this study: the intention-to-treat set (ITT), the per-protocol analysis set (PPS) and the safety analysis set (SAS). The ITT and PPS will be used to appraise the efficacy of TSF. If any given case exists missing a critical variable, the last observation used as the final results will be carried forward to the final data. The changes of urinary microalbumin–creatinine ratio, urinary microalbumin, GFR, creatinine and baseline information will be present after treatment. A paired *t* test or the Wilcoxon signed-rank test will be employed to compare each group. Changes relative to baseline after treatment will be compared between groups using the *t* test or the Wilcoxon rank-sum test. *P* < 0.05 will be deemed to show a statistically significant difference.

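### Negative conversion is defined as being below 20 μg/min with no abnormal baseline on that measure required, although patients may enter on ACR alone, so the treatment difference is diluted

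*Protocol article*

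**What the plan says.** **Outcome.** The Protocol article, Secondary outcomes, defines the negative conversion rate as "the ratio of normal urinary microalbumin", below 20 μg/min, compared between the two groups. The unit makes this an excretion rate. No baseline condition and no at-risk denominator is attached.

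**Entry.** Diagnostic criteria gives a UAER range of 30–300 mg/24 h, then "or urinary albumin-to-creatinine ratio (ACR) of" 30–300 mg/g. Either is enough. The inclusion criteria add no UAER floor, and the exclusion criteria remove nobody for a normal UAER.

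**Analysis sets.** Statistical analysis states: "The ITT and PPS will be used to appraise the efficacy of TSF". No subset with abnormal baseline UAER is named.

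**Abstract.** Methods/design lists "the rate of urine microalbumin negative conversion, the rate of normal urinary microalbumin" as two separate items. Secondary outcomes defines the one as the other.

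**Data collected.** In Table 1, "Urinary microalbumin excretion rate" is marked at screening/baseline and at every visit, as is the ACR.

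**The concern.** Conversion means moving from abnormal to normal. The printed definition counts the state after treatment only, so it measures how common normality is. The two coincide only if every patient is abnormal on the same measure at the start, and entry through the ACR route does not guarantee that.

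Patients who are normal on UAER at baseline and remain so add counts to the numerator of both arms and carry no information about conversion. The reported rate is then too high in each arm, the difference shrinks, and power for this outcome falls. The result may also be read as reversal of microalbuminuria in patients who had none on the measure used.

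**Working it through.** The article states no rate, sample size or power for negative conversion, so there is no figure of the plan's own to reproduce. The check has three parts.

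**1. Can a patient start below the conversion cut-off?**
- Conversion cut-off in daily units: 20 μg/min × 1440 / 1000 = 28.8 mg/24 h.
- UAER entry floor in μg/min: 30 × 1000 / 1440 = 20.8 μg/min.
- UAER route: the qualifying value is at least 20.8 μg/min, above the cut-off. The problem does not arise here.
- ACR route: there is no floor on UAER, so baseline UAER can be below 20 μg/min. If it is still below 20 μg/min after treatment, the patient meets the printed definition without having converted.

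**2. How much does this dilute the difference?**

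Let f be the share of patients with baseline UAER below 20 μg/min, s the share of those still below it at week 24, and c the true conversion rate among baseline-abnormal patients.

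Observed rate = f × s + (1 − f) × c

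None of these inputs is in the document. Assumed: c = 20% (control) and 30% (TSF); s = 80% in both arms; f = 5%, 15%, 25%.

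Worked case, f = 15%:
- Control: 0.15 × 0.80 + 0.85 × 0.20 = 0.120 + 0.170 = 29.0%
- TSF: 0.15 × 0.80 + 0.85 × 0.30 = 0.120 + 0.255 = 37.5%
- Difference 8.5 points; ratio 37.5 / 29.0 = 1.29

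| f | Control | TSF | Difference | Ratio |
|---|---|---|---|---|
| 0% | 20.0% | 30.0% | 10.0 points | 1.50 |
| 5% | 23.0% | 32.5% | 9.5 points | 1.41 |
| 15% | 29.0% | 37.5% | 8.5 points | 1.29 |
| 25% | 35.0% | 42.5% | 7.5 points | 1.21 |

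When s is the same in both arms, the term f × s cancels and the difference is (1 − f) × 10 points. The fall in the difference therefore depends on f alone; s affects only the level of the rates and their ratio.

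**3. Does restricting the denominator cost more than it gains?**

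The normal-approximation power of a two-sided 5% test of two proportions was computed with 275 per arm, the per-group number in the Sample size section. Restriction leaves 275 × (1 − f) per arm.

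| f | All patients (275 per arm) | Baseline-abnormal only (per arm) |
|---|---|---|
| 5% | 70% | 75% (261) |
| 15% | 56% | 71% (234) |
| 25% | 44% | 65% (206) |

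Under these assumptions the restricted comparison has more power although fewer patients are analysed.

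**The case against.** **The denominator may be in the SAP.** The word conversion implies an abnormal start, a separate detailed plan is said to exist, and an at-risk denominator is the kind of detail an article can leave to it. This has weight, but the article goes beyond naming the outcome: it gives a definition, and that definition is the proportion normal. A plan that follows it inherits the fault, and one that adds a baseline condition departs from the published text. The mismatch with the abstract stands either way.

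**The entry text is garbled.** One line of the Diagnostic criteria joins microalbuminuria and UAER with 'and', which might be read as requiring an abnormal UAER. The line that gives the ranges says 'or', and that is the operative criterion. How many patients lack an abnormal UAER cannot be read from the document.

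**Stronger readings that the document does not support:**
- *Baseline-normal patients count as converted regardless of treatment.* Only those who stay below 20 μg/min do. One who rises above it is not counted, and staying normal could itself be affected by treatment. Equal persistence in the arms is an assumption.
- *The outcome is biased toward TSF.* Randomisation should balance these patients on average. If they persist equally in both arms, the effect is toward no difference.
- *The gap between 28.8 and 30 mg/24 h is a defect.* It is not: the conversion cut-off lies below the UAER entry floor.
- *ACR and UAER are known to disagree often near the cut-off.* Nothing in the document says how often.
- *The outcome must move to ACR because "the urinary microalbumin–creatinine ratio (ACR) will be a primary evaluation index".* A secondary outcome need not share the primary's scale, and nothing in the document makes UAER the wrong measure.

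**Conclusion.** The point holds as a fault of definition. The stated rule measures normality, not conversion, and the ACR entry route lets in patients for whom the two differ. The consequence is an inflated rate in both arms and a diluted difference in one secondary outcome; the change in ACR, the primary outcome, is not affected.

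The size is unknown because the discordant share is not given. On the assumed rates the loss runs from 0.5 to 2.5 points of a 10-point difference for discordance of 5% to 25%. It is zero if no patient enters with UAER below 20 μg/min. The change is worth making because it is cheap and needs no new data.

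**What to change.** - **Definition.** Define negative conversion as UAER below 20 μg/min at week 24 among patients with baseline UAER of at least 20 μg/min, in the protocol and the SAP. This keeps the sponsor's measure and cut-off.
- **Optional support.** An ACR version (below 30 mg/g at week 24 among patients with baseline ACR of at least 30 mg/g) may be added as supportive. It is not needed to cure the fault, and it would leave out patients who entered on UAER with a lower ACR.
- **Abstract.** Either drop the separate rate of normal urinary microalbumin or give it its own definition, so that the abstract and Secondary outcomes list the same outcomes.
- **Reporting.** State in each arm how many patients had baseline UAER below 20 μg/min, so that readers can see the size of the excluded group.

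The cost is wording only, since both measures are already scheduled at baseline and every visit. The downside is a slightly smaller denominator, for example about 234 instead of 275 per arm at 15% discordance. On the assumed rates the undiluted difference more than makes up for it.

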#### Exclusion criteria

Proteinuria caused by non-DKD in the patient, such as gout, primary hypertension, tumors and proteinuria caused by chronic kidney diseaseCardiovascular, liver, kidney, hematopoietic system or other primary severe disease; serum transaminase more than double the standard value; serum creatinine (SCr) higher than the upper limit of normal; and psychiatric patientsPregnancy, preparation for pregnancy or lactation, or any history of drug allergyThe patient developed renal failure (anemia and uremia)Participation in another clinical trial or use of any other drug within the previous monthRecent use of ACEIs or ARBs except losartan in the past 1 monthAny excessive consumption of alcohol or any consumption of psychoactive substances, drug abuse or drug dependence during the past 5 yearsAccording to the researcher’s judgment, as some other diseases or conditions reduce the possibility of enrollment or complicate the enrollment, such as frequent changes of jobs and an unstable living environment, which may easily lead to loss of visits

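### The printed GFR formula attaches 1.154 to both creatinine and age, and neither reading of it gives usable GFR values or differences for the patients this trial admits

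*Protocol article*

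**What the plan says.** The protocol article names change in GFR as a secondary efficacy outcome, in the abstract and under Secondary outcomes. The outcome is defined as "change in the D-value and ratio of glomerular filtration rate (GFR) before and after treatment", compared between groups, so a difference and a ratio are both intended.

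The same entry says "GFR calculated using the simplified MDRD formula" and prints 186 as the leading constant, followed by "serum creatinine – 1.154 × age – 1.154" and then the factors "female × 0.742] × [Chinese × 1.233". No unit is given for creatinine. This is the only GFR definition in the article.

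The Inclusion criteria limit age to 30 to 70 years. The Exclusion criteria remove patients with "serum creatinine (SCr) higher than the upper limit of normal" and patients who have developed renal failure. Table 1 schedules serum creatinine and GFR at baseline and at every visit. The Statistical analysis section compares changes from baseline between groups by t test or rank-sum test.

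**The concern.** The text was read from PDF by a program, so a flattened superscript may explain why an exponent looks like a subtraction. It does not explain why one number appears on two different variables. One of the two must be wrong, or the eligibility criteria describe a different population from the one the formula implies.

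Absolute GFR and its change are stated efficacy results. If a derivation were programmed from this line, a baseline table for early-stage DKD could show values that belong to kidney failure, or changes with the wrong sign. The difference would also weight patients by an unintended function of age.

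**Working it through.** **Inputs from the document:** constant 186; the figure 1.154 on creatinine and on age; 0.742 for women; 1.233 for Chinese patients; age 30 to 70; creatinine not above the upper limit of normal; renal failure excluded.

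**Assumptions, because the document gives no figure or unit:** serum creatinine (SCr) of 0.6 to 1.2 mg/dl, with 0.4 to 1.4 mg/dl as a wider range; the same values in µmol/L (multiplied by 88.4) as an alternative unit. The sex factor is 1 for men. The article states no GFR value, so there is no figure to reproduce.

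**Reading 1: the figures are exponents.**

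GFR = 186 × SCr^(−1.154) × age^(−1.154) × 1.233 × (0.742 if female)

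| Patient | SCr (mg/dl) | GFR (ml/min/1.73 m2) |
|---|---|---|
| Man, 30 | 0.4 | 13.0 |
| Man, 30 | 0.5 | 10.1 |
| Man, 30 | 0.6 | 8.16 |
| Man, 50 | 1.0 | 2.51 |
| Man, 70 | 1.2 | 1.38 |
| Woman, 30 | 0.6 | 6.06 |
| Woman, 70 | 1.2 | 1.02 |
| Woman, 70 | 1.4 | 0.86 |

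For example, a man of 30 with SCr 0.6: 186 × 1.233 = 229.3; 0.6^(−1.154) = 1.803; 30^(−1.154) = 0.01974; the product is 8.16.

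The range is about 1.0 to 8.2 for 0.6 to 1.2 mg/dl and about 0.9 to 13 for 0.4 to 1.4 mg/dl. In µmol/L the largest value over the wider range is 0.074. Solving the formula for a GFR of 60 requires creatinine of about 0.04 to 0.11 mg/dl, depending on age and sex.

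**Reading 2: the minus signs are subtraction.**

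GFR = 186 × SCr − 1.154 × age − 1.154 × (sex factor) × 1.233

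For a man of 55:
- SCr 0.8: 148.8 − 63.5 − 1.4 = 84
- SCr 1.2: 223.2 − 63.5 − 1.4 = 158

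Creatinine worsens and GFR rises, so the direction is reversed for the difference and for the ratio.

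**Effect on the two versions of the outcome under reading 1.** Let SCr go from 1.0 to 1.1 mg/dl in a man.
- Ratio: 1.1^(−1.154) = 0.896 at any age. The age term cancels whatever its exponent, provided the same age is entered at both visits.
- Difference: baseline GFR × (0.896 − 1). At age 30, 4.53 × (−0.104) = −0.47. At age 70, 1.70 × (−0.104) = −0.18. The same creatinine change counts (70/30)^1.154 = 2.7 times as much in the younger man.

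**The case against.** The text names its method, and a misprint in a condensed article is a plausible explanation. Nothing in the document shows that a database or analysis program was built from this line. Single-digit GFRs in patients with normal creatinine would be noticed on first review. Serum creatinine is collected at every visit, so no information is lost. All of this stands. It limits the consequence and leaves the only printed definition wrong.

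On the between-group test, the distorting factor under the exponent reading depends only on age and acts alike in both arms. A randomised comparison of the differences therefore keeps its type I error. What is lost is the scale, the interpretation and possibly some power.

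A reader might go further than the document allows in three ways:

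- **That the whole GFR outcome is meaningless.** The ratio is half of the stated outcome and is unaffected under the exponent reading.
- **That every eligible patient would score 1 to 8.** That range needs mg/dl, an assumed creatinine range and the exponent reading. The article supplies none of these explicitly.
- **That GFR is understated by a definite multiple.** Any such figure needs the correct age exponent, which the article does not give. An exponent of −0.203 can be used as an illustration, but it is an assumption, and no result here rests on it.

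The missing creatinine unit alone could be left to the full protocol. It is mentioned only because the formula has to be restated anyway.

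**Conclusion.** The formula is wrong as printed. Under either reading it conflicts with the trial's own eligibility criteria, and this conclusion needs no outside source. Absolute GFR and the before-after difference are uninterpretable. Under the exponent reading the difference also carries an arbitrary age weighting, 2.7-fold between ages 30 and 70.

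The numerical ranges rest on the assumed creatinine values and unit. The conclusion does not, because every variant tried gave implausible values or the wrong direction. The primary ACR outcome, the creatinine-doubling outcome and the sample size do not depend on GFR. Whether the trial database carries the same error cannot be told from the article.

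**What to change.** Restate the named simplified MDRD equation with explicit exponents, giving age its own. Check every coefficient, including the sex and Chinese factors, and the creatinine unit against the source of the equation; the article alone cannot confirm them. Write the sex factor so that it applies to women only. State which age is used at follow-up visits.

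Then verify that any derivation in the electronic data capture system or the analysis programs uses the corrected equation, and re-derive GFR from the serum creatinine already collected at each visit. Do this before unblinding. The cost is one corrected formula and a programming check, with no new data, patients or visits.

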##### Safety assessment

Adverse events (AEs) will be continuously monitored for 24 weeks at the beginning and end of the study period, and the incidence of AEs will be evaluated at each visit, including vital signs, ECG, liver function, renal function, routine blood examination, routine urinalysis and routine stool examination. In addition, AEs, such as signs and symptoms and other ailments, will also be documented truthfully at every study visit, including the occurrence time, severity, duration, effective measures and transfer. Each AE associated with the intervention drugs will be classified as mild, moderate and severe. Severe AEs will need to be submitted to the Principal Investigator and the ethics committee within 24 h. All AEs will be properly resolved. Criteria for the severity of adverse events’ detailed requirements are as follows:
Mild: mild discomfort, subjects can endure no treatment, no special treatment is required, no effect on subjects’ recoveryModerate: moderate discomfort, unbearable to the subject, requiring special treatment, has a direct impact on the subject’s recoverySeverity: severe discomfort, life-threatening, fatal or disabling, immediate emergency treatment is required

### Study visits and assessment

The intervention cycle will be 24 weeks, including a run-in period. After the research commences, visits will occur every 4 weeks during the study period. An overview of specific measurements and time points for data collection is presented in Table 1.

**Table 1 Tab1:** Measurement items and point of data capture

Visit project	Screening period/baseline	Visits 1–2, 4–5	Visit 3	Visit 6
Visiting time	–7 to 0 days	Medication 4, 8, 16, 20 weeks ±7 days	Medication 12 weeks ±7 days	Medication 24 weeks ±7 days
Collect basic medical history				
Sign informed consent	×			
Fill in general information	×			
Medical history and treatment history	×			
Determine inclusion and exclusion criteria	×			
Vital signs	×	×	×	×
Physical examination	×	×	×	×
Comorbidity and medication records	×	×	×	×
Monitoring and inspection				
Urine pregnancy test	×			
Glycosylated hemoglobin, blood lipids	×		×	×
Fasting blood sugar and blood pressure	×	×	×	×
Effectiveness observation				
Urinary microalbumin–creatinine ratio	×	×	×	×
Urinary microalbumin excretion rate	×	×	×	×
Serum creatinine	×	×	×	×
Glomerular rate filtration	×	×	×	×
24-h urinary microalbumin and 24-h urinary microalbumin quantification	×		×	×
Physico-chemical examination				
Routine blood test and routine urine test	×		×	×
Stool routine examination	×		×	×
Vital signs	×	×	×	×
ECG, liver and kidney function	×		×	×
Adverse event		×	×	×
Other work				
Random grouping	×			
Distribute drug and patient journal cards	×	×	×	
Recovery drugs, quantity statistics		×	×	×
Recycle patient’s diary card		×	×	×
End of study summary				×

*ECG* electrocardiogram

